#### Measures of psychological resilience

2.6.1

##### Connor-Davidson resilience scale

2.6.1.1

The CD-RISC (34, 35) is a 25-item questionnaire examining attitudes toward coping with adversity. The shorter, 10-item questionnaire is being administered for this study. The CD-RISC is the primary outcome measure for this study.

##### Dispositional recovery and dysfunction inventory

2.6.1.2

The DRDI (36) is a 14-item measure comprised of two subscales (recovery and dysfunctional cognitions). Participants rate themselves concerning their perception of themselves on a Likert scale of 1 (not at all characteristic of me) to 7 (entirely characteristic of me).

##### Response to stressful experiences scale

2.6.1.3

The RSES (37) is a 22-item questionnaire that asks participants to assess how well each statement describes them, both during and after stressful events in their lives.

#### Measure of trait resilience

2.6.2

##### Short grit scale (Grit-S)

2.6.2.1

The Grit-S (38) is an eight-item grit scale that examines trait-level perseverance and passion for long-term goals. Participants are asked to rate themselves on items such as “My interests change from year to year” or “I am a hard worker” on a Likert scale ranging from “not at all like me” to “very much like me.”

#### Measures of psychological flexibility

2.6.3

##### Acceptance and action questionnaire-II

2.6.3.1

The AAQ-II (39) is a seven-item measure of experiential avoidance and psychological inflexibility. Participants are asked to rate themselves on items such as “Emotions cause problems in my life” on a Likert scale of 1 (never true) to 7 (always true).

##### Multidimensional psychological flexibility inventory

2.6.3.2

The MPFI (40) is a 60-item measure of the six core processes underlying the ACT psychological flexibility model. Each core process is rated in terms of both flexibility and inflexibility. For each of the six core processes, there are six items reflecting flexibility (acceptance, present moment awareness, self-as-context, cognitive defusion, values, and committed action) and six items reflecting inflexibility (experiential avoidance, lack of contact with the present moment, self-as-content, cognitive fusion, lack of contact with values, and inaction).

#### Measure of self-efficacy

2.6.4

##### General self-efficacy questionnaire–6

2.6.4.1

The GSEQ-6 (41) is a six-item, self-report measure that assesses general self-efficacy as related to an individual’s ability to adapt to stressful events.

#### Measure of mindset

2.6.5

##### Implicit theories of intelligence scale

2.6.5.1

The Dweck ITIS (42, 43) is a six-item, self-report scale examining individual fixed/growth mindsets concerning intelligence. Participants are asked about their agreement on a 6-point Likert scale from 1 (strongly agree) to 6 (strongly disagree) to items such as, “You have a certain amount of intelligence, and you really cannot do much to change it.”

#### Measure of life satisfaction

2.6.6

##### Quality of life scale

2.6.6.1

The QOLS (44) is a 16-item, self-report measure of life satisfaction during the past year in 16 life domains, including health, participation in community and relationships, and creative expression. Items are rated on a scale from 1 (delighted) to 7 (terrible).

#### Measures of psychological health

2.6.7

##### Generalized anxiety disorder-7 scale

2.6.7.1

The GAD-7 (45) is a seven-item measure that asks participants to rate the frequency with which they have been bothered by anxiety symptoms within the past 2 weeks on a scale ranging from 0 (not at all) to 3 (nearly every day).

##### PTSD checklist for DSM-5

2.6.7.2

The PCL-5 (46) is a 20-item, self-report measure of PTSD symptoms, with higher scores reflecting greater PTSD severity. Scoring is based on how much the patient has been bothered by the symptoms in the past month on a scale from 0 (not at all) to 4 (extremely).

##### Patient health questionnaire-9

2.6.7.3

The PHQ-9 is a widely used and well-validated measure of depressive symptoms (47, 48). It consists of nine items that correspond to the DSM diagnostic criteria for major depressive disorder. Respondents rate the frequency with which they have been bothered by depressive symptoms within the past 2 weeks. Respondents also indicate the degree to which their depressive symptoms have made it difficult for them to do their work, take care of things at home, or get along with other people.

#### Measure of unit cohesion

2.6.8

##### Walter reed army institute of research (WRAIR) horizontal and vertical cohesion

2.6.8.1

The WRAIR cohesion scales (49, 50) are the established method of evaluating attitudes about support from peers (horizontal) and leaders (vertical). Horizontal cohesion is assessed using three items, and vertical cohesion is assessed using 13 items. Participant agreement to these 16 statements is rated on a 5-point scale (1 = “strongly disagree” to 5 = “strongly agree”). Individuals answer the questionnaire for their current unit.

#### Measure of family functioning

2.6.9

##### General functioning 12-item subscale (GF12) of the McMaster family assessment device (FAD)

2.6.9.1

The GF12 is a 12-item, self-report measure that is a subscale of the FAD (51, 52) designed to assess family functioning. The GF12 subscale includes six items assessing healthy family functioning and six items assessing unhealthy family functioning. Participants are asked about their agreement on a 4-point Likert scale from “strongly agree” to “strongly disagree” to items such as “Planning family activities is difficult because we misunderstand each other” and “In times of crisis we can turn to each other for support.”

#### Evaluation and feedback about training

2.6.10

##### Qualitative interview

2.6.10.1

Focus groups will be semi-structured interviews conducted approximately 2 weeks after the training. These groups are designed to assess participants’ perceptions of the training and to solicit recommendations for future training modifications. Qualitative data collected during the focus groups will be recorded and analyzed using a method like that described in the 2015 New Hampshire Medicaid Management Focus Groups (53). Notes and recordings will be transcribed and analyzed for common themes.

### Data analytic plan

2.7

The primary outcome to address study aims is the change score difference between group (psychological flexibility vs. treatment as usual) on the Connor-Davidson Resilience Scale (CD-RISC) over time. Analyses will be intent-to-treat using data from all randomized participants regardless of the extent of participation. The statistical analysis model is a mixed-effects regression with repeated measures using all assessment time points. Advantages of likelihood-based regression models over conventional ANOVA include the ability to use data from all participants even if they only have baseline data, relaxation of the assumption of equal variances, specification of data distributions other than normal, and the ability to analyze longitudinal data in the presence of missing data. Models will include the fixed effects of group, time, and the respective two-way interaction. Deployment history will also be entered into models as a covariate. Random intercepts and slopes will be tested, and covariance structure selection will be based on likelihood criteria model comparisons (e.g., Akaike’s Information Criteria). Little’s (1988) missing completely at random test and regression-based sensitivity analyses will be used to investigate the nature of missingness and the appropriateness of likelihood-based modeling (54). We will also derive and report on minimally important difference metrics on the CD-RISC (55, 56). Supplementary analyses of the other measures will use the same statistical analysis design. We will report on minimally important change and reliable change indices for the Posttraumatic Stress Disorder Checklist-5 (PCL-5), for which these metrics have been established (55, 57). We will assess deployment history at all time-points and will use this as a covariate in all pre-post analyses. All tests will be two-tailed with unadjusted *p* = 0.05. Analyses will be done using the LME4 package using R statistical software.

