#### Randomization

2.2.1

Recruited personnel will be randomized as a group to Resilience Enhancement through Acceptance and Commitment Training (REACT) or regular programming. Group randomization will be completed prior to recruitment or consent. Groups will be randomized by a randomization list generated by the research team’s Biostatistics Core. The randomization list will use random blocks of 4, 6, and 8 to ensure roughly equal numbers of groups in each condition as the study progresses and to reduce the anticipation of group assignment and thereby the potential for bias.

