### Recruitment & randomization

2.4

Soldiers are recruited through briefings at various unit meetings as well as at the unit’s Newcomers’ Briefing held monthly. Any soldier, 18 years or older, is eligible for inclusion. There are no exclusion criteria. Participants are equally randomized between the two groups stratifying for rank to ensure equal numbers of junior non-commissioned officers (NCOs; grades E-4 to E-6), senior NCOs (grades E-7 to E-9), and officers (warrant and commissioned) are in each group. In accordance with Department of Defense (DoD) Instruction 3216.02, participants can be compensated if study participation does not adversely impact their ability to perform their assigned duties. Five assessments are scheduled. Each time an assessment is completed, $25 can be compensated, for a total of $125.

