#### Power analysis

2.7.1

Statistical power estimates were obtained from the PASS15 software (NCSS, 2017) modules for comparison of two means or two proportions in a cluster randomized design. Estimates were obtained for a range of standardized mean differences (Cohen’s *d*) from 0.35 to 0.50, which range from modest (*d* = 0.35) to medium in size (*d* = 0.50). Effect sizes below 0.35 are unlikely to be clinically significant and *d* = 0.50 is often considered to be a threshold for a meaningful difference. We also estimated the reduction in Failure % that was detectable at 0.80 assuming a base rate of 80%. We specified a total of 12 clusters of 50 participants for a total *N* = 600. The proposed sample size (*N* = 600) provides statistical power of at least 80% to detect a standardized mean difference (or change over time) in the “small to moderate” range (Cohen’s *d* of 0.30). This applies not only to analyses involving the entire randomized sample but also for analyses based on subsamples based on factors such as deployment, demographics, or other military service characteristics.

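### Groups are randomized and power assumes 12 clusters, but the primary model need not contain the randomized unit, so the group-by-time test may not respect the randomization

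*Protocol article*

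**What the plan says.** Section 2.2.1 (Randomization): "Recruited personnel will be randomized as a group to Resilience Enhancement through Acceptance and Commitment Training (REACT) or regular programming". It adds "Group randomization will be completed prior to recruitment or consent".

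Section 2.7.1 (Power analysis) relies on software "modules for comparison of two means or two proportions in a cluster randomized design" and states "We specified a total of 12 clusters of 50 participants", which makes up the 600. It claims at least 80% power at a Cohen's d of 0.30. It gives no ICC.

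Section 2.7 (Data analytic plan) takes the between-arm difference in CD-RISC change as the primary outcome and tests it two-sided at 0.05. On the model: "Models will include the fixed effects of group, time, and the respective two-way interaction". Group here means the trial arm, as the section's own parenthesis shows. Deployment history is a covariate. On random effects: "Random intercepts and slopes will be tested, and covariance structure selection will be based on likelihood criteria model comparisons", with Akaike's criterion as the example. The level of these effects (participant or unit) is not named, and neither a unit nor a cluster is mentioned. The other measures are to be analysed in the same way.

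Section 2.4 (Recruitment & randomization) reads differently on allocation: "Participants are equally randomized between the two groups stratifying for rank".

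**The concern.** When groups are allocated, the evidence on the training effect comes from comparing groups. The test must therefore measure the arm difference in change against how much change varies between groups. A model with participant-level effects only measures it against variation between soldiers. That understates the standard error whenever units drift apart over time. Such drift is plausible here, because soldiers share a unit and the workshop is fitted into the unit's training calendar (section 2.8).

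The design and power sections recognise clustering, but the analysis section does not oblige the analyst to. At stake is a training without effect being declared effective on the primary outcome, with confidence intervals that are too narrow. The secondary measures inherit the same model.

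**Working it through.** **Inputs.** From the article: 12 clusters of 50, 300 per arm, two-sided alpha 0.05, d = 0.30, power at least 80%. Assumed: 6 clusters per arm (from 300 versus 300) and the ICC of change, for which the article gives no value.

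**1. The stated power.** Without clustering, SE(d) = √(2/300) = 0.0816. Then 0.30/0.0816 = 3.67 and power = Φ(3.67 − 1.96) = 95.7%. With clustering, the variance is multiplied by the design effect DE = 1 + (50 − 1) × ICC. The 80% claim cannot be reproduced as one figure without an ICC, but it can be solved for one. Power at d = 0.30 is at least 80% up to ICC 0.0147 with a normal reference (DE 1.72), or up to 0.0081 with t on 2 × (6 − 1) = 10 df (DE 1.40).

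**2. Type I error if clustering is ignored.** The test statistic has true standard deviation √DE instead of 1, so the actual error is 2 × [1 − Φ(1.96/√DE)].

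| ICC of change | DE | naive SE / true SE | actual type I error |
|---|---|---|---|
| 0 | 1.00 | 1.00 | 5.0% |
| 0.005 | 1.245 | 0.90 | 7.9% |
| 0.0081 (limit, t) | 1.40 | 0.85 | 9.7% |
| 0.01 | 1.49 | 0.82 | 10.8% |
| 0.0147 (limit, normal) | 1.72 | 0.76 | 13.5% |
| 0.02 | 1.98 | 0.71 | 16.4% |

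**3. Which ICC matters.** A simulation of the five-wave group-by-time comparison (12 clusters of 50, 4,000 runs per scenario, participant-level effects only) rejected in 11.1% and 17.6% of runs at a slope ICC of 0.01 and 0.02. This agrees with step 2. With a stable difference in level between units and no difference in slope, it rejected in 5.5%, which is nominal within simulation error. A constant unit effect cancels from a change contrast; only unit-by-time variance inflates the error. A cluster-level t test on 10 df stayed between 4.7% and 5.3% throughout.

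**4. If the unit effect is a candidate term.** Here balanced 12 × 50 change scores were simulated under REML, keeping the unit variance only when AIC favours it.
- The term is kept about 30%, 55% and 90% of the time at ICC 0.01, 0.02 and 0.05.
- Rejection is about 6% to 9%, depending on the ICC and on whether t or normal critical values are used when the term is kept.
- If the term is always in the model but referred to a normal distribution, error is about 6% to 8%. The upper limit is P(|t₁₀| > 1.96) = 7.8%.
- Always kept with the unit mean square and 10 df, it is 5.0%.

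**The case against.** A reader might infer that the planned analysis ignores clustering and that its type I error is therefore well above 5%. The document does not establish that, for four reasons.

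- The random effects in section 2.7 have no stated level, so they could include the unit. The authors used a cluster-randomized power module and plainly knew of the clustering. This is a condensed article; details such as the denominator df may stand in a fuller plan that is not shown.
- No ICC is given, and only the unit-by-time part matters for a change contrast. At zero the error is nominal. An ICC of 0.05 would give 29.1%, but that ICC, like 0.02, lies above what the stated power at d = 0.30 allows.
- Section 2.4 reads as allocation of individuals stratified by rank. If that is what happens, clustering would come mainly from shared units and group workshops, and the figures above would not apply in full.
- Twelve clusters is a planning figure. The realized number and size of groups may differ, so the 10 df are provisional. The AIC simulation used single change scores, and AIC is only the article's example of a criterion.

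These limit the size and certainty of the inflation. They do not remove the defect. Section 2.7 is not silent: it states the fixed effects and a selection rule for the random effects, and under that rule the randomized unit is either absent or optional. Even on the favourable reading, with the unit as a candidate term, selection by fit leaves the error above 5% at ICC 0.01 to 0.05.

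**Conclusion.** The point holds as a missing commitment. Sections 2.2.1 and 2.7.1 describe a cluster-randomized trial; the model in section 2.7 does not require the randomized unit. If units differ in their change over time, the primary test is anti-conservative.

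The size depends on an ICC that the document does not give. With clustering ignored, error runs from nominal at ICC 0 to about 16% at 0.02, and is about 10% to 13.5% at the ICC limits implied by the stated power. With the unit selected by AIC it is about 6% to 9%; with the unit always kept but a normal reference, about 6% to 8%. All of this assumes that groups are the unit of allocation, with about 12 groups of 50 split evenly. It should be settled before analysis, because it affects the validity of the primary p-value and costs little to correct.

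**What to change.** 1. Reconcile sections 2.2.1 and 2.4, and state whether groups or participants are randomized and where rank stratification enters.
2. If groups are the unit, state in section 2.7 that every model contains a random intercept and a random change over time (unit-by-time) for the randomized unit, both kept whatever the fit criteria say. An intercept alone is not enough for a change contrast.
3. Restrict AIC-type selection to the within-person structure.
4. Test the treatment contrast with small-sample degrees of freedom based on the number of randomized units (about 10 if there are 12), for example Satterthwaite or Kenward-Roger. A permutation test is optional; if used, it must follow the actual blocked group allocation.

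The cost is a change of wording, with wider confidence intervals and lower nominal power. With 10 df, power at d = 0.30 is about 91% at ICC 0, 84% at 0.005, 77% at 0.01 and 65% at 0.02. The 80% statement in section 2.7.1 should therefore be restated with its assumed ICC.

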### Measures

2.6

Ideally, resiliency enhancement training for military personnel demonstrates not only improvements in self-reported resiliency and other related constructs but also demonstrates positive adaptation in the face of significant stress or adversity as a result of the training (33). Related to this, the present study examines a range of resilience-related constructs (i.e., dispositional recovery, stress response, and grit) and correlates (dysfunctional cognitions, depression, and anxiety). Given our theoretical approach, we anticipate that resilience-related outcomes would be associated with increased psychological flexibility (16). The schedule of assessments is outlined in Table 1. A brief description of each measure is provided below. A more detailed description of each measure including information on validity and reliability of each measure is included in Supplement 1. Administered assessments address the constructs of psychological resilience, trait resilience, psychological flexibility, self-efficacy, mindset, life satisfaction, psychological health, unit cohesion, family functioning, and evaluation and feedback about the training (see Table 1).

**Table 1 tab1:** Schedule of assessments involved in the Resilience and Readiness Optimization/Enhancement (R2OE) study.

Construct	Assessment	Number of items	Baseline	Every 4 months
Psychological resilience	Connor-Davidson Resilience Scale (CD-RISC)	10	X	X
	Dispositional Recovery and Dysfunction Inventory (DRDI)	14	X	X
	Response to Stressful Experiences Scale (RSES)	22	X	X
Trait resilience	Short Grit Scale (Grit-S)	8	X	X
Psychological flexibility	Acceptance and Action Questionnaire-II (AAQ-2)	7	X	X
	Multidimensional Psychological Flexibility Inventory	60	X	X
Self-efficacy	General Self-Efficacy Questionnaire–6 (GSEQ-6)	6	X	X
Mindset	Implicit Theories of Intelligence Scale (ITIS)	6	X	X
Life satisfaction	Quality of Life Scale	16	X	X
Psychological health	Generalized Anxiety (GAD-7)	7	X	X
	PTSD Checklist (PCL-5)	20	X	X
	Patient Health Questionnaire-9 (PHQ-9)	9	X	X
Unit cohesion	Walter Reed Army Institute for Research (WRAIR) Military Vertical and Horizontal Cohesion Scale	15	X	X
Family functioning	General Functioning Scale (GF12)	12	X	X
Evaluation and feedback about training	Qualitative Interview			2-weeks after training

Assessments will be conducted at baseline and every 4 months thereafter for a total of 16 months.

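### Little's MCAR test is given the job of checking the likelihood-based CD-RISC model, but that model rests on missing at random, which the test cannot assess

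*Protocol article*

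**What the plan says.** All the analytic statements are in section 2.7, Data analytic plan.

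- Outcome: "The primary outcome to address study aims is the change score difference between group" on the CD-RISC over time.
- Model: "The statistical analysis model is a mixed-effects regression with repeated measures using all assessment time points". Among the reasons for a likelihood-based approach the section lists "the ability to analyze longitudinal data in the presence of missing data".
- Missing data: Little's "missing completely at random test and regression-based sensitivity analyses will be used" "to investigate the nature of missingness and the appropriateness of likelihood-based modeling".

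The section names neither MAR nor MNAR. It does not say what the regression-based sensitivity analyses consist of, or what would follow from a significant or non-significant test. Deployment history is collected at every time point and enters the models as a covariate.

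Follow-up is set out under Table 1 in section 2.6, Measures: "Assessments will be conducted at baseline and every 4 months thereafter for a total of 16 months". That gives five time points.

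**The concern.** A named test is given a purpose that it cannot serve. The null hypothesis of Little's test is MCAR: missingness unrelated to any score, seen or unseen. A likelihood-based mixed model makes the weaker assumption that missingness is unrelated to the unseen scores once the observed data are taken into account. The two assumptions come apart in both directions.

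- **False alarm.** If soldiers with low observed scores drop out more often, MCAR is false and the test should reject. The model can still be unbiased.
- **False reassurance.** If dropout in one arm depends on the part of the current score that earlier scores do not predict, earlier means are alike in those who stay and those who leave. The test then has nothing to detect, and the model is biased.

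What is at stake is the argument for robustness. Follow-up lasts 16 months, deployments vary in timing and length, the outcome is self-reported, and only one arm attends a two-day workshop. Dropout related to resilience, and differing by arm, is plausible. In that setting a non-significant Little's test could be offered as support for the primary result although it gives none.

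**Working it through.** The plan gives no figure to reproduce, so the check is by logic and simulation.

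**Inputs from the protocol article.** 600 participants, so 300 per arm; baseline plus four follow-ups; two-sided 0.05; d = 0.30 (section 2.7.1, Power analysis).

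**Assumptions not in the article.** Within-person correlation 0.6; normal scores with SD 1; monotone dropout; clustering ignored; the dropout models below. The sizes depend on these choices.

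**A. Two waves, true effect 0, 2,000 trials per scenario.** Follow-up is y1 = 0.6·y0 + e, and the SD of e is √(1 − 0.6²) = 0.8. With two waves and dropout only at the second, Little's statistic reduces to comparing baseline means of completers and dropouts (chi-square, 1 df). The effect comes from the baseline-adjusted likelihood model.

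- MAR: logit P(missing) = −1.45 − 0.5·y0 in both arms.
- MNAR: logit P(missing) = −1.6 − 1.0·e in the intervention arm and −1.4 in control.

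The MNAR bias can be found without simulation. With expit(x) = 1/(1 + exp(−x)) and φ the normal density of e with SD 0.8:

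- Intervention missing fraction: p = ∫ expit(−1.6 − e) φ(e) de = 0.195.
- Control missing fraction: expit(−1.4) = 0.198.
- Bias = mean of e among those observed in the intervention arm = ∫ e·[1 − expit(−1.6 − e)] φ(e) de / (1 − p) = 0.113 SD.
- Relative to the stated effect: 0.11 / 0.30 = 0.37, over a third.

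Simulated results from two independent runs of this design:

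| Dropout | Little rejects | Bias of model |
|---|---|---|
| MAR (depends on y0) | 99.8%, 99.7% | 0.00 SD |
| MNAR (depends on e, one arm) | 5.0%, 6.5% | +0.11 SD |

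With one-arm dropout depending instead on the total current score, the test rejected in about 74% of trials.

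**B. Five visits, true change difference 0.30, 1,000 trials per scenario.** The estimate is multivariate-normal maximum likelihood by arm. Little's test is run on the pooled data, and by arm with Bonferroni correction.

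| Dropout | Little rejects (pooled / by arm) | Estimate | Estimate − 0.30 | Missing at month 16 (control / intervention) |
|---|---|---|---|---|
| MCAR | 4.1% / 4.1% | 0.301 | 0.00 | 34% / 34% |
| MAR, previous observed score | 100% / 100% | 0.300 | 0.00 | 41% / 36% |
| MNAR, unpredicted part of current score, one arm | 6.0% / 4.2% | 0.504 | +0.20 | 34% / 47% |
| MNAR, same, last visit only | 5.4% / 4.5% | 0.553 | +0.25 | 27% / 33% |
| MNAR, total current score, one arm | 74.7% / 97.6% | 0.394 | +0.09 | 34% / 34% |

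**Reading.** Rejection occurs with no bias (MAR) and with bias (MNAR through the total score). Non-rejection occurs with no bias (MCAR) and with bias (MNAR through the unpredicted part). Neither result says whether the model is appropriate.

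**The case against.** Four points can fairly be made for the plan.

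1. **Little's test is not the only tool.** The sentence pairs it with regression-based sensitivity analyses. A reader might infer that these use observed data only, so that nothing probes MNAR. The text does not support that: it gives no form for them, and the source it cites is not at hand. Regression-based analyses can include pattern-mixture terms or shifted imputations. If they do, the false-reassurance side is covered. Even so, the MCAR test would still be a poor guide to whether the likelihood model is appropriate.
2. **There is no decision rule.** A reader might infer that the model will be kept or dropped on the test result. Nothing says so: the tools are there to investigate, and no estimate changes because the test is run. This stands, and it limits the harm.
3. **The MNAR example is built to defeat the test.** In the two-wave case, dropout depends only on a term independent of baseline, so rejection near 5% follows by construction. Other MNAR forms are rejected often (about 74–98%). This stands as a limit on the size of the bias. It does not rescue the test, since rejection there looks the same as under harmless MAR.
4. **Detail belongs elsewhere.** A journal article may leave shift sizes and MNAR methods to the full protocol or SAP, and their absence is not held against it. The point concerns only what the article does state: the purpose given to a named test. Likewise, deployment history as a covariate may account for part of any deployment-related dropout, though only the part explained by recorded deployment.

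**Conclusion.** The point holds in a limited form. Little's test addresses a stricter assumption than the mixed model needs. It can reject when the model is unbiased, and stay at its nominal level when dropout is MNAR and the model is biased. The consequence is a misleading justification of robustness, not a certain error in the primary estimate.

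The two-way failure follows from the definitions of MCAR, MAR and MNAR and does not depend on the simulation. The sizes do. The +0.11 SD is one constructed case with assumed correlation 0.6, about 20% missing, two waves and no clustering. The five-visit biases of +0.09 to +0.25 rest on equally assumed dropout models, with 27–47% missing at month 16. A reader might take these as the bias to expect in this trial; the article gives no dropout rate, correlation or dropout mechanism from which to predict one. A correction is worth making because the present wording invites a reassurance that the test cannot give.

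**What to change.** Amend the missing-data sentence in section 2.7 in three ways.

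1. State that the primary mixed model assumes MAR given the observed CD-RISC scores and the model's covariates.
2. Keep Little's test, if wanted, as a description of the missingness pattern only, and remove its link to the appropriateness of the likelihood model.
3. Say what the sensitivity analysis for CD-RISC is: a delta-adjusted (tipping-point) multiple imputation or a pattern-mixture analysis with separate shifts by arm, for example 0 to −0.5 SD in the intervention arm. Report it whatever any missingness test shows. If the planned regression-based analyses already do this, saying so is enough.

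The cost is a change of wording and at most one extra analysis on data already being collected. Design, sample size and primary model stay as they are.

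### The hypothesis 1 model conditions on deployment occurring after randomization, and its change-score contrast uses baseline CD-RISC less efficiently than covariate adjustment would

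*Protocol article*

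**What the plan says.** All of the modelling text is in the protocol article, section 2.7 (Data analytic plan).

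- Target: "The primary outcome to address study aims is the change score difference between group" on the CD-RISC over time. The analysis is declared intent-to-treat.
- Model: "The statistical analysis model is a mixed-effects regression with repeated measures using all assessment time points". One advantage claimed for it is "the ability to use data from all participants even if they only have baseline data", so baseline CD-RISC is one of the modelled responses.
- Terms: "Models will include the fixed effects of group, time, and the respective two-way interaction". Then: "Deployment history will also be entered into models as a covariate".
- Timing of that covariate: "We will assess deployment history at all time-points and will use this as a covariate in all pre-post analyses".

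Section 2.7.2 (Addressing hypotheses) describes hypothesis 1 as the pre-post training effect in everyone randomized, and restricts hypothesis 2 to those who deployed. Section 2.2.1 (Randomization) has groups randomized before recruitment or consent. Section 2.4 (Recruitment & randomization) says: "Participants are equally randomized between the two groups stratifying for rank". Rank is not among the model terms listed in section 2.7.

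**The concern.** There are two separate issues.

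**Deployment as a covariate.** A deployment history updated at every assessment includes deployments that begin after assignment. Such deployments are to be expected: the first unit deploys on a regular schedule, and assessments run for 16 months. An intent-to-treat comparison estimates the total effect of assignment. Holding fixed something that happens later targets a different quantity if assignment can influence it. The article neither separates earlier from later deployment nor says which quantity hypothesis 1 is meant to estimate.

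**Use of baseline.** A group-by-time contrast with a free group effect at baseline is a difference in mean change. It is a valid estimator, but it subtracts the whole baseline score, whereas regression on baseline subtracts only the predictive part. The standard error is therefore larger than the same data allow, in a trial planned with only 12 clusters.

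**Working it through.** **The plan's own figure.** Section 2.7.1 (Power analysis) claims at least 80% power at d = 0.30 with 12 clusters of 50. The article gives no intracluster correlation (ICC), so no single figure can be reproduced. With ICC 0, power is 95.7% (normal reference) or 91.1% (t with 12 − 2 = 10 df). It stays at 80% or more for ICC up to about 0.015 (normal) or 0.008 (t). Neither issue depends on this claim, but it shows that precision is not in surplus.

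**Deployment covariate.** All inputs are assumed, since the article gives none: direct training effect 0.30, deployment effect −0.3 SD, about 50% deployed, and training shifting the deployed proportion by *a*.

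- Total effect of assignment = 0.30 − 0.3 × *a*. For *a* = 0.10 this is 0.30 − 0.03 = 0.27.
- Effect at fixed deployment = 0.30. The gap is 0.03 SD, and 0.03 / 0.30 = 10% of the target effect.
- Reversed shift, *a* = −0.10: the total is 0.30 + 0.03 = 0.33 against 0.30 adjusted. Adjustment now lowers the estimate.

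A simulation with 2,000,000 records per scenario, with and without an unmeasured common cause of deployment and CD-RISC, gave:

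| Shift in deployment | Total effect | Adjusted, no common cause | Adjusted, common cause |
|---|---|---|---|
| 0 | 0.30 | 0.30 | 0.30 |
| 5 points | 0.29 | 0.30 | 0.29 |
| 10 points | 0.27 | 0.30 | 0.28 |
| 20 points | 0.24 | 0.30 | 0.26 |

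The first row matters as much as the others: with no effect of arm on deployment, adjustment does no harm.

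**Baseline CD-RISC.** Let r be the baseline-to-follow-up correlation (assumed), with equal variances and one follow-up. In units of the score variance:

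- Change score: 2(1 − r)
- Baseline as covariate: 1 − r²
- Ratio: (1 − r²) / [2(1 − r)] = (1 + r)/2
- Reduction in SE: 1 − √[(1 + r)/2]

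| r | Variance ratio | SE reduction |
|---|---|---|
| 0.3 | 0.65 | 19.4% |
| 0.5 | 0.75 | 13.4% |
| 0.6 | 0.80 | 10.6% |
| 0.7 | 0.85 | 7.8% |
| 0.8 | 0.90 | 5.1% |

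One simulated data set (n = 600, r = 0.6) confirmed the equivalence. The group-by-time mixed model and the plain change score both gave 0.2298 with SE 0.0734. Baseline as a covariate gave SE 0.0669 (1 − 0.0669/0.0734 = 8.9% smaller), and a model with a common baseline mean gave SE 0.0654 (10.9% smaller).

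As an illustration for the cluster design, take ICC 0.01, 10 df, r = 0.5 and d = 0.30 in score SDs. Power rises from 77% to 88%. This assumes that the same design effect applies to both estimators, which the article cannot confirm.

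**Rank.** A rank main effect that is constant over time cancels from a within-person change. If rank explained 1% to 5% of residual variance (assumed), 1 − √0.99 = 0.5% and 1 − √0.95 = 2.5% would come off the SE.

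**The case against.** Several stronger readings are tempting, and the document does not support them.

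- *That the hypothesis 1 estimate is biased.* This needs training to alter deployment or its reporting. The article describes scheduled deployments and gives no reason to think a two-day workshop changes them. The objection stands: the risk is conditional.
- *That deployment is the pathway through which training works, or is mainly a property of the unit.* The article places the mechanism in psychological flexibility and treats deployment as the setting in which hypothesis 2 is tested. Section 2.7.2 refers to each participant's own deployment dates.
- *That baseline CD-RISC is ignored.* It is in the model as a response, and baseline differences are subtracted out. What is left is a choice between valid estimators.
- *That baseline means are equal by design, so a common baseline mean can be imposed.* Groups are randomized before recruitment and consent, so the recruited arms may differ. This is why covariate adjustment is preferable here to the slightly more precise common-mean model.
- *That leaving out rank invalidates the comparison.* In a linear model it does not bias the arm contrast. Section 2.2.1 also describes group randomization without mentioning rank, so it is unclear how the stratification in section 2.4 operates.

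Two further defences are fair. Deployment may predict CD-RISC, so adjusting for it could reduce noise or correct a chance imbalance; that supports a labelled secondary analysis. And section 2.7.2 confines hypothesis 1 to four months either side of training, which would limit how much later deployment enters. However, section 2.7 uses all time points, and section 2.2 (Design) frames the first hypothesis over the course of the study.

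An unseen SAP may refine the covariate list. The deployment rule is nevertheless stated in the article and covers every pre-post analysis, so it is a choice and not an omission.

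**Conclusion.** The point holds in two limited parts. First, the stated rule puts deployment occurring after randomization into an intent-to-treat model. The consequence is a possible departure from the total effect of assignment, of unknown sign: about 0.03 SD under the assumed 10-point shift and 0.3 SD deployment effect, and zero if training does not affect deployment or its reporting. Second, the group-by-time contrast is less precise than covariate adjustment by about 5% to 19% in SE for assumed r from 0.8 to 0.3. That figure is for individuals with one follow-up; the gain in the clustered, multi-visit analysis may differ. Rank is a minor refinement. The case for changing the plan is that the conditional risk can be removed, and the precision gained, using data already collected.

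**What to change.** 1. In the hypothesis 1 model, define deployment history as that recorded at the baseline assessment, before training. Use deployment during follow-up only for hypothesis 2 or in an analysis labelled exploratory.
2. Model post-baseline CD-RISC scores with baseline CD-RISC as a covariate. The training effect is then the adjusted group difference at the prespecified post-training visit, not the interaction with baseline. Baseline should not stay in the response as well, or it would be used twice.
3. Optionally add rank category as a fixed effect.

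The cost is wording in the plan, settled before outcome data are examined by arm; every variable is already collected. One consequence needs stating: participants with only a baseline score no longer enter this model, so the sentence claiming their inclusion needs revising and their number by arm should be reported.
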